## Abstract

**Background:**

Neuromyelitis Optica spectrum disorder (NMOSD) is severe relapsing and disabling autoimmune disease of the central nervous system. Its optimal first-line treatment to reduce relapse rate and ameliorate neurological disability remains unclear. We will conduct a prospective, multicenter, randomized, placebo-controlled clinical trial to study the safety and effectiveness of human umbilical cord mesenchymal stem cells (hUC–MSCs) in treating NMOSD.

**Methods:**

The trial is planned to recruit 430 AQP4-IgG seropositive NMOSD patients. It consists of three consecutive stages. The first stage will be carried out in the leading center only and aims to evaluate the safety of hUC—MSCs. Patients will be treated with three different doses of hUC–MSCs: 1, 2, or 5 × 10^6^ MSC/kg·weight for the low-, medium-, and high-dose group, respectively. The second and third stages will be carried out in six centers. The second stage aims to find the optimal dosage. Patients will be 1:1:1:1 randomized into the low-, medium-, high-dose group and the controlled group. The third stage aims to evaluate the effectiveness. Patients will be 1:1 randomized into the optimal dose and the controlled group. The primary endpoint is the first recurrent time and secondary endpoints are the recurrent times, EDSS scores, MRI lesion numbers, OSIS scores, Hauser walking index, and SF-36 scores. Endpoint events and side effects will be evaluated every 3 months for 2 years.

**Discussion:**

Although hUC–MSC has shown promising treatment effects of NMOSD in preclinical studies, there is still a lack of well-designed clinical trials to evaluate the safety and effectiveness of hUC–MSC among NMOSD patients. As far as we know, this trial will be the first one to systematically demonstrate the clinical safety and efficacy of hUC–MSC in treating NMOSD and might be able to determine the optimal dose of hUC–MSC for NMOSD patients.

**Trial registration:**

The study was registered with the Chinese Clinical Trial Registry (CHICTR.org.cn) on 2 March 2016 (registration No. ChiCTR-INR-16008037), and the revised trial protocol (Protocol version 1.2.1) was released on 16 March 2020.

## Introduction

Neuromyelitis Optica spectrum disorder (NMOSD) is a severe disabling inflammatory autoimmune disease of the central nervous system (CNS) featured with recurrent relapses of optic neuritis and longitudinally extensive transverse myelitis (1). Autoantibodies against the water channel protein aquaporin-4 (AQP4) are the diagnostic markers of the disorder and more than two-thirds of patients meeting clinical criteria for NMOSD are AQP4-IgG seropositive (2, 3). Frequent relapses are associated with a stepwise accumulation of neurological disability. Therefore, relapse prevention is particularly important to reduce the risk of a systemic disability over time (4). Azathioprine and mycophenolate mofetil are the most commonly used therapies for patients with NMOSD (5, 6). Recently, some randomized clinical trials show that the use of B-cell depletion (rituximab, inebilizumab), interleukin-6 signaling blockade (tocilizumab, satralizumab), and complement inhibition (eculizumab) can reduce the risk of relapses in NMOSD (7–11). However, still, some patients who have had these therapies have relapsed. So far, the optimal first-line treatment to reduce relapse rate remains unclear. Furthermore, no drug has been proved to improve neurological disability in NMOSD patients.

Stem cells are a group of cells that are immortal and have unlimited renewal abilities. The types of stem cells usually used in the registered clinical trials include multipotent stem cells, hematopoietic stem cells, and mesenchymal stem cells. There are some pilot trials and cohort studies assessing the therapeutic effect of stem cell transplantation in NMOSD patients (12–14). Recently, autologous nonmyeloablative hematopoietic stem cell transplantation showed to be effective on prolonged drug-free remission with AQP4-IgG seroconversion to negative (12).

Mesenchymal stem cells (MSCs) are stromal precursor cells residing in many tissues, including bone marrow, umbilical cord (UC), fetal liver, and adipose tissue (15–17). MSCs are considered to be multipotent and have anti-inflammatory, immune regulation, and paracrine effects, and also regenerative properties (18). MSCs derived from the human umbilical cord (hUC–MSCs) are more primitive, and possess multiple advantages including ethical agreeableness, a less-invasive procedure for isolation, low immunogenicity, high-proliferation capacity, and multi-lineage differentiation capability (19, 20). Therefore, hUC–MSCs are a promising candidate for cell-based therapy.

Treatment with MSC improves the course of the preclinical model of multiple sclerosis, experimental autoimmune encephalomyelitis (EAE) when administered at the early stages. In EAE, MSC has a profound anti-inflammatory and immune-modulating effect, but they also exhibit neuroprotective features and foster remyelination endogenous neurogenesis with scarce evidence of differentiation in neural cells (21–23). A pilot clinical trial showed that infusion of autologous MSC derived from bone marrow is safe, can reduce the relapse frequency, and mitigates neurological disability with the recovery of neural structures in the optic nerve and spinal cord in NMOSD patients (24).

Human umbilical cord–MSCs can regulate the immune response, promote tissue repair, and increase regeneration both *in vitro* and *in vivo* (25). Therefore, we suggest that hUC–MSCs can prevent relapses and ameliorate disability in NMOSD. However, as far as we know, there are very few reports on the use of hUC–MSCs in NMOSD patients. Here, we present the protocol of Human Umbilical Cord Mesenchymal Stem Cells to Treat Neuromyelitis Optica Spectrum Disorder (hUC–MSC–NMOSD), a prospective, multicenter, randomized, and placebo-controlled clinical trial. The main aims of the study are to verify that the hUC–MSCs can prolong the relapse interval, reduce the relapse times and ameliorate the neurological disability in NMOSD patients.

## Methods and Analysis

### Setting and Participants

The study will be conducted in six clinical centers in Shanghai, China. The leading center is Shanghai Ren Ji Hospital, which is one of the main teaching hospitals of the Shanghai Jiao Tong University School of medicine. Ren Ji Hospital is also one of the biggest clinical centers of neuroimmunological disorders in China. The five branch centers are Shanghai Rui Jin Hospital, Shanghai Xin Hua Hospital, Shanghai General Hospital, Shanghai Sixth People's Hospital, and Shanghai Ninth People's Hospital. In this study protocol, only the patients who fulfilled the diagnostic criteria of NMOSD established by Wingerchuk et al. (26) will be included.

The study protocol has been approved by the Ethics Committees of Ren Ji Hospital (2016-071K).

Patients will be recruited from those neuro-immunological centers of Neurology departments in China. Eligible patients will be invited to participate. All the participants will receive adequate information about the nature, purpose, possible risk, and benefits of the trial, and about alternative therapeutic choices. A signed written informed consent form will be obtained from all the participants before enrollment.

The clinical study will be conducted in accordance with all the national regulations and complies with the principles of the World Medical Association Declaration of Helsinki—Ethical Principles for Medical Research Involving Human Subjects, with all its amendments, and also with the principles of Good Clinical Practice.

The clinical information collected including age, sex, past medical history, NMOSD attack time and frequency, corrected visual acuity by standard logarithmic visual acuity chart, Expanded Disability Status Scale (EDSS) score, Opticospinal Impairment Scale (OSIS) score, Hauser walking index, quality of life short Form-36 (SF-36) score, serum status of anti-AQP4 antibody (tested in a cell-based assay), laboratory tests as listed in Table 1, electrocardiogram, abdominal ultrasound, chest X-ray or computed tomography, optical coherence tomography, number of brain and spinal cord lesions on MR images, immunomodulatory drugs used in the past 6 months, etc.

**Table 1 T1:** Schedule of activities of human umbilical cord mesenchymal stem cells (hUC–MSCs) to treat neuromyelitis optica spectrum disorder (hUC–MSC–NMOSD) study.

**Follow-up Period**	**V0** **(Screening)**	**V1** **(Baseline)**	**V2**	**V3**	**V4**	**V5**	**V6**	**V7**	**V8**	**V9**
Time	**−30 ~ −1d**	**0**	**3M ± 7d**	**6M ± 7d**	**9M ± 7d**	**12M ± 7d**	**15M ± 7d**	**18M ± 7d**	**21M ± 7d**	**24M ± 7d**
General characteristics	√									
Inclusion and exclusion criteria	√									
Informed consent	√									
Physical examination	√		√	√	√	√	√	√	√	√
EDSS score	√		√	√	√	√	√	√	√	√
OSIS score	√		√	√	√	√	√	√	√	√
Hauser walking index	√		√	√	√	√	√	√	√	√
SF-36 score	√		√	√	√	√	√	√	√	√
Exploratory endpoints associated tests	√		√	√	√	√	√	√	√	√
Complete blood counts	√		√	√	√	√	√	√	√	√
Urinalysis	√		√	√	√	√	√	√	√	√
Coagulation function	√		√	√	√	√	√	√	√	√
Liver and kidney function	√		√	√	√	√	√	√	√	√
Serum glucose	√		√	√	√	√	√	√	√	√
Serum electrolyte	√		√	√	√	√	√	√	√	√
Thyroid function	√									
Urine HCG	√		√	√	√	√	√	√	√	√
Tests for infective diseases	√				√					√
Tumor markers	√		√	√	√	√	√	√	√	√
EKG	√		√	√	√	√	√	√	√	√
Abdominal ultrasound.	√		√	√	√	√	√	√	√	√
Chest X-ray or CT	√		√	√	√	√	√	√	√	√
MRI (head)	√					√				√
MRI (spinal cord)	√					√				√
MRI (optical nerve)	√					√				√
OCT	√					√				√
Primary treatment	√	√	√	√	√	√	√	√	√	√
hUC-MSC or placebo treatment		√	√	√	√					
Record of AE		√	√	√	√	√	√	√	√	√
Record of combined medications	√		√	√	√	√	√	√	√	√

### Study Design

This is a prospective study for an open-labeled, prospective, multicenter, randomized, placebo-controlled clinical trial. The estimated study period is from March 2019 to March 2025. The NMOSD patients in the remission phase will be randomized into two groups: the treatment group (hUC–MSC infusion plus regular treatment) and the controlled group (stem cell base solution infusion plus regular treatment). All the patients will be treated and followed up for 2 years.

The whole clinical trial includes three consecutive stages.

The first stage of the trial, which will last 24 months, is an open-labeled study and will be carried out in the leading center only. The first stage aims to evaluate the safety of the infusion of hUC–MSC in NMOSD patients. Patients (*n* = 30) will be treated with three different doses of hUC–MSC. According to the process of enrollment, the first to the tenth participant is in the low-dose group (*n* = 10, 1 × 10^6^ MSC / kg·weight); the eleventh to the twentieth participant is in the medium-dose group (*n* = 10, 2 × 10^6^ MSC / kg·weight); the twenty-first to the thirtieth participant are in the high-dose group (*n* = 10, 5 × 10^6^ MSC / kg·weight). The study starts from the low dose. Only when the lower dose group ends the observation period of 3 months, the study will proceed to a higher dose group. In case of unacceptable toxic reaction occurs in the dose escalation, the study will be ended immediately. In relation to safety considerations, before enrolling the patients in the low-dose group, we will give a single medium dose of hUC–MSC to one patient and follow-up the therapy for one year. The outcome of this dosage will be used only for safety evaluation, not to evaluate the therapy's effectiveness.The second and third stages of the study protocol are part of the multi-center double-blinded randomized clinical trial. The second stage, which aims to screen out the optimal dosage, will last for 24 months and will be carried out in six centers (one leading center and five branch centers). Patients (*n* = 160) will be randomized into four groups: the low-, medium-, high-dose groups, and the controlled group (*n* = 40, respectively). In the second stage, we were seeking to determine the ‘optimal biological dose.’ The dose that allows reaching the optimal efficacy-toxicity trade-off is further selected and recommended to stage 3. The third stage, which aims to evaluate the effectiveness, will last for 24 months and will be developed in six centers. Patients (*n* = 320) will be randomized into two groups: the optimal dose group (*n* = 160) and the controlled group (*n* = 160). The third stage aims to evaluate the effectiveness and safety of hUC–MSC for NMOSD patients. The study flow chart is shown in Figure 1.

**Figure 1 F1:**
[figure not shown]
Study flow chart of human umbilical cord mesenchymal stem cells to treat neuromyelitis optica spectrum disorder (hUC-MSC-NMOSD) study.

### Inclusion Criteria

1) 18–75 years of age;2) Met the diagnostic criteria of NMOSD (established by the International Panel for NMOSD in 2015) (26), and serum AQP4-antibody-positive;3) In the remission phase, defined as no new or worsening of neurological symptoms and signs in the last 30 days;4) EDSS (Expanded Disability Status Scale) score ≤ 8;5) Taking azathioprine or mycophenolate mofetil as ongoing treatment for NMOSD;6) The results of the hepatic and renal function tests, complete blood count, and urinalysis are unremarkable;7) The coagulation tests are unremarkable;8) Be able to end the follow-up period;9) Signed the informed consent (by patients or their families).

### Exclusion Criteria

1) Patients with language dysfunction, disturbance of consciousness, or unstable vital signs;2) With thyroid dysfunction or other endocrine dysfunction which cannot be controlled by treatment;3) With severe psychiatric disorders, thus unable to cooperate during the study;4) With severe hepatic or renal disorders: the results of hepatic function >2 upper limits; the creatinine clearance rate calculated by Cockcroft–Gault equation <60 ml/min; or with severe systematic wasting diseases;5) Scoring complete blood count test, white blood cell count test <3.0 × 10^9^/L or >12 × 10^9^/L, or hemoglobin level <80% lower limits, or platelet counts <100 × 10^9^/L;6) Scoring coagulation tests, one or multiple indicators (TT, APTT, PT, FIB, TDP, and DD) >2 upper limits;7) Gastrointestinal bleeding or other severe bleeding disorders in the last month;8) Had allergic history to the study-related drugs;9) Had major surgeries in the last week;10) Pregnant or breastfeeding;11) With a history of hepatitis B, hepatitis C, HIV infection, syphilis, or malignancies;12) With other rheumatic diseases (such as Sjogren's syndrome, systematic lupus erythematosis), who need to use other immunodepressants other than azathioprine or mycophenolate mofetil;13) With other situations that may affect the patient's engagement in the study.

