### Group Allocation, Randomization, and Blinding

The first phase of the trial is an open-label, dose-escalation study that will be performed in a leading center, the Shanghai Ren Ji Hospital. For stages 2 and 3, allocation sequences were generated by an independent statistician by permuted blocks randomization method (block sizes of four or eight). The conceal of allocation sequences were performed by using an integrated web response system (IWRS). The research physician will enroll participants and then assign participants to interventions according to allocation results from IWRS. In stage 2, there are four arms, which are the low dose group (1 × 10^6^ MSC / kg·weight), the medium dose group (2 × 10^6^ MSC / kg·weight), the high dose group (5 × 10^6^ MSC / kg·weight), and the control group (stem cell base solution). Patients will be assigned randomly in a 1:1:1:1 ratio to hUC–MSC groups and control group, respectively. In stage 3, there are two treatment arms. Patients will be assigned randomly in a 1:1 ratio to the hUC–MSC group and control group, respectively. To avoid ethical problems, we designed an add-on trial. Patients in the placebo-controlled group will receive a placebo while they already receive an established regular treatment (azathioprine or mycophenolate mofetil). Therefore, the allocation ratio of 1:1 was based on optimal statistical power and add-on trial design. In stages 2 and 3, all the participants, investigators, and statistician are blinded to group allocation until the end of the study and data analysis. Only pharmacists who are in charge of preparing study drugs are not blinded. Double-blinding will be performed *via* a centralized randomization system. Subjects who leave the study after random allocation will not be replaced.

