Lan–DeMets alpha-spending function with an O'Brien–Fleming boundary will be used to control the family-wise of type I error. Inverse normal combination test will be used to combine data from stages 2 and 3 in the final analysis. An independent Data and Safety Monitoring Board (DSMB) will review and evaluate the accumulated study data for participant safety, study conduct, and progress at each stage of the study. Only members of DSMB could have access to the data and results of the analysis. The Ethics Committee will be notified of any amendment to the study protocol. DSMB can make recommendations to terminate the study based on one of the following conditions: a significant difference in terms of effectiveness between groups; a significant risk-benefit ratio in one group; low degree of success in a reasonable period (such as poor compliance, low incidence of endpoint events). The advice of the DSMB meeting will be shared with the steering committee of the trial.

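### The eligibility rules admit patients with other recent or concurrent relapse-preventing NMOSD treatment, or earlier stem-cell treatment, which does not fit an add-on comparison over azathioprine or mycophenolate

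*Protocol article*

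**What the plan says.** Inclusion criterion 5 (Inclusion Criteria) requires "Taking azathioprine or mycophenolate mofetil as ongoing treatment for NMOSD". It does not say that this must be the patient's only relapse-preventing treatment.

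Exclusion criterion 12 (Exclusion Criteria) is the only one on other immunosuppressants. It opens with a condition, "With other rheumatic diseases (such as Sjogren's syndrome, systematic lupus erythematosis", and then restricts itself to those patients "who need to use other immunodepressants other than azathioprine or mycophenolate mofetil". Criterion 13, the catch-all, reads "With other situations that may affect the patient's engagement in the study".

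The Introduction lists B-cell depletion, interleukin-6 blockade and complement inhibition as treatments that "can reduce the risk of relapses in NMOSD". Setting and Participants has the sites collect "immunomodulatory drugs used in the past 6 months", but no criterion uses that information.

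Study Design describes hUC-MSC or base solution, each given with regular treatment, in three consecutive stages, with the leading centre in all of them. Group Allocation, Randomization, and Blinding calls this an add-on trial in which controls "receive a placebo while they already receive an established regular treatment (azathioprine or mycophenolate mofetil").

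**The concern.** The comparison is meant to show what hUC-MSC adds to azathioprine or mycophenolate. The listed criteria leave two routes by which a patient can enter with some further protection against relapse.

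- **Other NMOSD immunotherapy.** A biologic taken alongside the background drug, or stopped shortly before entry, lowers the relapse risk in whichever arm the patient joins. Events are lost, and the population is no longer one treated with azathioprine or mycophenolate alone.
- **Earlier hUC-MSC or other cell therapy.** A participant who has finished stage 1 or 2, and is still seropositive, on background drug and in remission, can meet the listed criteria again and be allocated to control.

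At stake are the power of the final comparison, what its result describes, and to a smaller degree the choice of dose in stage 2.

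**Working it through.** **1. The criteria side by side.** Take an AQP4-positive patient in remission, on mycophenolate plus a biologic for NMOSD, without another rheumatic disease. Inclusion 5 is met. Exclusion 12 does not apply, because its condition fails. Exclusion 13 concerns engagement, not treatment history. No other item among the 9 inclusion and 13 exclusion criteria mentions biologics, a washout, cell therapy or earlier participation. The same holds for someone who has completed stage 1 or 2.

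**2. The plan's own figure.** Inputs from Sample Size Estimation: relapse 55% against 40%, two-sided 5%, 80% power, 20% loss, 400 patients. HR = ln(0.60)/ln(0.45) = 0.640. Schoenfeld's formula gives 158 events. 158/0.475 = 333 patients, and 333 × 1.2 = 400, so the figure is reproduced. With 20% lost, 320 remain. Power is then 78.6% by Schoenfeld's formula and 76.9% by a two-proportion test with 160 per arm.

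**3. Controls carrying an hUC-MSC effect (shares assumed).** Suppose a share f of controls has the 40% risk. Control risk is 0.55(1 − f) + 0.40f, so the difference is 0.15(1 − f).

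- Simple version, variance held, starting from 80%: power = Φ(2.80(1 − f) − 1.96). For f = 10%, the difference is 13.5 points and power is Φ(0.56) = 71%. For f = 20%, it is 12 points and Φ(0.28) = 61%.
- Two-proportion test, 320 evaluable, starting from 76.9%: 72.6% at f = 5%, 67.9% at 10%, 57.7% at 20%.

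**4. Biologics in both arms (shares and effect assumed).** Suppose a share g of each arm uses a biologic that halves relapse risk. Both risks are multiplied by 1 − g/2. At g = 20% they become 0.495 and 0.36. Expected events among 320 fall from 320 × 0.475 = 152 to 320 × 0.4275 = 137. Power is 72.8% at g = 10%, 68.6% at 20% and 64.3% at 30%. With a 70% risk reduction it is 71.2%, 65.2% and 59.1%.

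**5. Chance imbalance in stage 2.** With 20% users and 40 per arm, the standard deviation of the difference in user share between two arms is √(2 × 0.2 × 0.8/40) = 0.089. If a biologic halves a risk of 0.55, an imbalance of that size moves the relapse difference by 0.089 × 0.275 = 0.025. The standard error of the relapse difference itself is √((0.55 × 0.45 + 0.40 × 0.60)/40) = 0.110. The imbalance is real but small beside ordinary sampling error.

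**6. How many could re-enter.** Study Design exposes 30 stage 1 patients, one patient treated before the low-dose group, and 3 × 40 = 120 stage 2 patients: 151 at most. A 10% share of controls would mean about 32 re-entrants among 320 under 1:1 allocation, or 32/151 = 21% of everyone exposed. A 20% share would mean 64, or 42%.

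**The case against.** **Inclusion 5 may already fix the NMOSD treatment.** Read with the add-on description, it can be taken to mean azathioprine or mycophenolate and nothing else, with exclusion 12 closing the remaining route through a second disease. That is probably the intention, but the words do not say so, and the condition on exclusion 12 points the other way. Recently stopped biologics remain unaddressed even on this reading.

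**Re-entry is not planned.** Nothing says that earlier participants will be enrolled again. By Table 1 the last infusion is at 9 months and follow-up ends at 24, so someone who completes follow-up is about 15 months past treatment, and no passage supports a full effect lasting that long. This stands: the shares in the calculation are illustrations.

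**The article is condensed.** A full protocol exists and may be more explicit. But the article prints numbered criteria in detail, down to laboratory limits, and the wording of exclusion 12 is itself the difficulty. An IWRS duplicate check could well be left to the full protocol.

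**Stronger readings that a reader might infer.**

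- That a patient in both stages invalidates the analysis in which "Inverse normal combination test will be used to combine data from stages 2 and 3 in the final analysis". This does not follow. Stage 3 has its own 1:1 randomisation. If hUC-MSC has no effect, the fresh assignment is independent of the stage 2 data, and the stage 3 statistic stays centred on zero given those data.
- That the totals prove overlap. The stage sizes give 160 + 320 = 480 against the stated 400, a gap of 80. This would fit 80 stage 2 patients counted again among the 320, but equally a total of 400 that omits the two unselected dose arms. The article does not say which.
- That the trial claims an effect in patients never given hUC-MSC. It claims only an add-on effect over regular treatment.

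**Conclusion.** The gap is real on the text and worth closing. As written, the criteria admit patients with other recent or concurrent relapse-preventing NMOSD immunotherapy and do not exclude earlier stem-cell treatment or earlier-stage participation, which is inconsistent with the stated add-on comparison.

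The exposure precedes randomisation and is balanced in expectation. The harm is therefore dilution, fewer events, lower power and some chance imbalance in stage 2. A systematic bias between arms, which a reader might infer, is not supported.

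The size is unknown, because the article gives neither the frequency of biologic use nor any expected re-entry. Under the assumed shares, nominal 80% power falls to about 71% if 10% of controls carry a full hUC-MSC effect. With 20% of both arms on a biologic that halves risk, 76.9% falls to 68.6%. Partial carry-over or smaller shares would cost less.

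**What to change.** For stages 2 and 3:

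1. Reconcile exclusion 12 with inclusion 5 and the add-on design, so that it covers other relapse-preventing NMOSD immunotherapy whether or not the patient has a rheumatic disease. The drug history already collected for the past 6 months can support this. The length of any look-back is for the investigators to set.
2. Exclude earlier stem-cell treatment, including participation in an earlier stage.
3. State that stage 2 and stage 3 patients are distinct people, and reconcile 400 and 430 with the stage sizes of 30, 160 and 320.
4. Have the IWRS reject anyone already randomised.

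The cost is one reworded criterion, one added criterion, one sentence and one system check, with a somewhat smaller recruitment pool in the six centres. It needs an amendment. Trial Quality Assurance allows one only after a serious adverse event, whereas Statistical Analysis provides for notifying the Ethics Committee of any amendment, so that restriction should be settled at the same time.
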